**Figure 1 F1:**
[figure not shown]
**SINS study design overview**.

Extra clinic visits can be arranged if participants are concerned about adverse reactions or progress. Those participants developing a brisk inflammatory response to imiquimod to the extent that they find it difficult to continue can follow a pre-defined schedule of rest periods and reduced dosing frequency. These participants will be analysed with the main data with an appropriate sensitivity analysis.

### Randomisation

One lesion per patient will be chosen for the study, so that the unit of analysis will be patients rather than tumours. For those patients with multiple suitable BCCs, the research nurse will pick one *before *randomisation as below:

• The one that the patient is most bothered about, or first went to the doctor about

• If that does not apply, or the tumour in question does not meet the criteria, then the one that is easiest for the patient to reach.

• If this applies to more than one, the biggest will be chosen.

• If the patient wants both nodular and superficial BCCs treated, then a nodular BCC should be chosen to ensure there is enough cream for all (i.e. 12 weeks rather than six weeks of cream). If it happens that the histology shows the chosen nodular lesion not to be a BCC, but a superficial one is (assuming it had a biopsy), then the patient should be withdrawn, and re-randomised by the superficial BCC list.

Other current BCCs may be treated in the same way as the randomised one if the patient wishes, but this option should only be offered if needed, and BCCs are clinically suitable.

The identified BCC will be biopsied (three centres biopsy post randomisation, this being part of surgery for the surgery group). Patients eligible for inclusion and for whom consent has been obtained will be randomised to topical imiquimod or surgery, according to a pre-prepared randomisation schedule, generated by computer at the Trent Research and Development Support Unit (Trent RDSU). The allocation is obtained at the baseline visit, using a central telephone randomisation service run by independent staff at the Trent RDSU. This ensured concealment of allocation.

Randomisation will be stratified according to lesion type (nodular or superficial, defined clinically) and by centre, thus minimising the differences in the most important predictor baseline variables. There will be no attempt to equalise numbers of nodular and superficial BCCs randomised.

The participant's general practitioner and consultant will be informed about the participant's involvement in the study.

To minimise selection bias the allocation sequence will be concealed from participants, healthcare staff and investigators - the allocated treatment only being obtained after the participant had decided to take part in the trial (though the participant is always free to withdraw from the study at any time). Masking of the two very different interventions will not be possible for participants, and only partially possible for observers. We will determine whether there is evidence of dermatologists' observer bias at the 3 year visit by asking an independent panel of 3 dermatologists to judge "clinical success" from digital photographs.

The trial and full protocol are registered with the Cochrane Skin Group Ongoing Trials Register [http://www.nottingham.ac.uk/ongoingskintrials/ NB protocol not accessible from Cochrane], and with the UK meta-register of trials. Consumers with BCC have already been and will continue to be involved in commenting on the study design and conduct.

### Sample size

Based on initial Phase II data, it is highly unlikely that imiquimod cream will be superior to excisional surgery, so this is essentially a *non-inferiority study *i.e. the imiquimod success rate will be no worse than a pre-determined lower acceptable level.

The original total sample size estimate was for 740 participants, to be recruited over 18 months in three centres. This assumed a 1-tailed significance with (alpha) = 1%, power (1-β) = 80%, a 3 year success rate with surgery of 97% and for imiquimod of 90%, a lower 98% confidence limit of 84%, and allowed for a 10% drop-out rate. An imiquimod success rate of 90% was generally considered the lowest percentage to *change dermatologists' practice*, assuming success rates approaching 90% for other commonly used treatment modalities such as cryotherapy or curettage. The estimate is conservative, considering imiquimod as a direct competitor to surgery or other treatments, as opposed to using the cream first and then surgery if it fails i.e. sequential technology application.

Due to recruitment being slower than expected (many BCCs in high risk areas and the trial was too time consuming for potential participants), nine more centres were added and the recruitment period extended to 42 months; later (March 2006) the sample size was revisited. Various scenarios were considered. For a sample size of 500 the lower confidence interval would be within less than 10 percentage points of the actual imiquimod success rate assuming imiquimod success rate is at least 70% - probably acceptable precision for influencing practice. The revised overall sample size of 500 is considered to be both useful and achievable.

### Statistical analysis

The primary efficacy analysis will be performed using both a Full Analysis Set and the Per Protocol Set of participants. All other efficacy analyses will use the Full Analysis Set only. Data will be analysed using Stata version 10.1. No adjustments will be made for multiple endpoints. There is only one primary outcome variable. Secondary outcome variable findings and subgroup analysis findings will be interpreted with caution in view of the number of statistical tests undertaken.

Participants in the three centres performing the biopsy post-randomisation, and who were found not to have a BCC, did not continue in the study; they will be excluded from the analysis.

An independent Data and Safety Monitoring Committee reviewed data with the trial statistician relating to severe skin reactions.

**An early stopping rule** was proposed to safeguard participants with nodular BCC against unacceptably low early clearance rates from imiquimod however, due to the higher proportion of superficial BCCs than expected, all participants were recruited before the planned number of participants for the interim look were recruited, so the assessment was not made.

**Sub group analyses** are to be performed only for the primary outcome measure. These will assess whether the effectiveness of imiquimod cream in comparison to surgery is different in participants with:

• nodular lesions and those with superficial BCCs (confirmatory analysis)

• trunk lesions and those with head lesions (exploratory analysis)

• lesions ≤15 mm diameter and those with lesions greater than 15 mm diameter (exploratory analysis)

For each of the above analyses sensitivity analyses will be performed including and excluding participants with BCCs who are immunosuppressed at baseline.

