### Trial interventions

1. Imiquimod 5% cream once daily for 6 (superficial - clinically diagnosed) or 12 (nodular) weeks total, or

2. Surgical excision with a 4 mm margin (accepted standard at trial set-up). The surgical group will be operated on as soon as local conditions permit.

Treatment failures (after either a biopsy or a period of watchful waiting) will be treated by surgical excision. Treatment duration and frequency of dosing are based on results of existing studies [15] at study set-up, and a balance of efficacy with effort for the participants and possible side effects. The dosing frequency was unchanged after the manufacturers presented results from a large dose-finding clinical study to us, however after the start of this study imiquimod became licensed for superficial BCC, with a 5 days per week dosing frequency.

In order to identify possible genetic markers for tumour response, 5 ml of blood will be taken from consenting participants. Methods for analysing the genetic marker data are given in a separate genetic markers addendum to the protocol.

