#### Inclusion criteria

• Men and women of any age who present clinically with either primary nodular or superficial BCCs, or a skin lesion other than BCC which turns out on histology to be a superficial or nodular BCC

• Any number of BCCs (although only one per participant is selected for the study)

• Histologically proven BCC (usually a punch or shave biopsy specimen of no more than 25% of the total lesion, though sometimes at surgery)

• Location of primary nodular/superficial BCC in low risk areas (avoiding use of imiquimod in areas at high risk of recurrence where delay of appropriate surgery might result in more invasive procedures)

• Informed consent

• Must have access to a telephone

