#### Exclusion criteria

• Genetic or nevoid conditions such as Gorlin's syndrome

• Morphoeic (microinfiltrative) trial lesion as diagnosed clinically (even if not histologically classed as morphoeic - histological sample may have missed infiltrative nature of lesion)

• Allergy to any of the interventions

• Involvement in a trial of another experimental intervention

• Life threatening disease

• Bleeding disorders

• Not available for follow up for 3 yrs

• Pregnant, intention to become pregnant during treatment phase of the trial, or breastfeeding

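### At three of the 12 centres, post-randomisation exclusion of non-BCC participants rests on histology obtained differently by arm, and no analysis described in the article tests the effect

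*Protocol article*

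**What the plan says.** Histologically proven BCC is an inclusion criterion. The Inclusion criteria describe the evidence as "usually a punch or shave biopsy specimen of no more than 25% of the total lesion, though sometimes at surgery". Under Randomisation the article states that "three centres biopsy post randomisation, this being part of surgery for the surgery group". Surgery is excision with a 4 mm margin (Trial interventions).

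The Statistical analysis section then fixes what follows: "Participants in the three centres performing the biopsy post-randomisation, and who were found not to have a BCC, did not continue in the study", and "they will be excluded from the analysis". The same section names the sets for the primary outcome: "The primary efficacy analysis will be performed using both a Full Analysis Set and the Per Protocol Set of participants". The Non inferiority margin paragraph calls the comparison of sets intention to treat against per protocol.

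A related rule under Randomisation covers a patient who wants lesions of both types treated. If the chosen nodular lesion proves not to be BCC but a biopsied superficial one is, "then the patient should be withdrawn, and re-randomised by the superficial BCC list".

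**The concern.** Removing ineligible participants after randomisation is harmless when eligibility is a pre-treatment fact established in the same way in both arms. Here the fact is pre-treatment, but the way it is established follows allocation. At three centres, surgery-arm histology arrives with the operation, while cream-arm histology needs a separate sample. If that sample is partial, it can miss a BCC that an excision specimen would show. Genuine BCC participants would then leave the cream arm and not the surgery arm.

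At stake is the non-inferiority comparison, judged by whether the lower 98% confidence limit of the relative risk (RR) exceeds 0.87. If those wrongly removed would have done worse than the rest of the cream arm, the RR is too favourable to cream; if better, too unfavourable.

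**Working it through.** **Which described analyses could reveal the effect?**

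- Worst- and best-case runs (Missing data paragraph): these are for missing outcomes. The participants in question are excluded, not missing.
- Agreement of intention-to-treat and per-protocol results: the exclusion is stated without distinction between sets, so it acts on both and cannot separate them.
- Runs with and without immunosuppressed participants: unrelated.
- Centre as a covariate: it adjusts for differences in level between centres, not for selective removal within one. The nine smallest centres are also pooled, and the article does not say whether the three centres are among them.

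**The plan's own figures.** Margin: 0.84 / 0.97 = 0.866, stated as 0.87. Original sample size, taking 1:1 allocation: (2.326 + 0.842)² × (0.97 × 0.03 + 0.90 × 0.10) / (0.13 − 0.07)² = 332.03, so 333 per arm and 666 in total; 666 / 0.9 = 740. Both agree with the article and neither is disputed.

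**Illustrative shift in the RR.** Let p be true 3-year success among all cream-arm BCC participants, x the share wrongly excluded, and q the success rate those excluded would have had. Surgery stays at 97%.

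Observed RR = [(p − xq) / (1 − x)] / 0.97

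The article gives neither x nor q. I assume that the three centres hold 10% to 50% of participants and that a partial sample misses 5% to 20% of BCCs. So x runs from 0.10 × 0.05 = 0.5% to 0.50 × 0.20 = 10%. With p = 0.84 (true RR 0.866):

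| x | q = 50% | q = 100% |
|---|---|---|
| 0.5% | 0.868 | 0.865 |
| 2.5% | 0.875 | 0.862 |
| 5% | 0.884 | 0.857 |
| 10% | 0.905 | 0.848 |

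Worked cell (2.5%, q = 50%): (0.84 − 0.0125) / 0.975 = 0.8487; 0.8487 / 0.97 = 0.875.

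The shift runs from about −0.02 to +0.04. A lower q gives more: at x = 2.5% and q = 0, 0.84 / 0.975 = 0.8615, a shift of +0.022. With p = 0.90 (true RR 0.928) and x = 2.5%, the observed RR is 0.938 (q = 50%) or 0.925 (q = 100%).

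**Against sampling error.** With 500 × 0.9 / 2 = 225 per arm and success of 84% and 97%, the standard error of log RR is √[(0.16/0.84 + 0.03/0.97) / 225] = 0.031. The shift from 0.866 to 0.875 is ln(0.875 / 0.866) = 0.010, about a third of that.

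**What a bound would look like.** Assume 25% to 50% of participants are at these centres (about 62 to 125 per arm) and 5 percentage points more are excluded from cream than from surgery: 0.05 × 62 = 3 to 0.05 × 125 = 6 extra exclusions. About 225 × 0.10 = 22 cream failures are expected. Counting the extra exclusions as cream failures, with 225 × 0.90 = 202.5 successes, gives 202.5 / 228 = 0.888 (RR 0.916) for 3 and 202.5 / 231 = 0.877 (RR 0.904) for 6, against 0.928 without them.

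**A bound to avoid.** Take 25 excluded per arm, 225 left, success 84% and 97%. Counting all excluded as successes gives (189 + 25) / (218.25 + 25) = 0.880, against 189 / 218.25 = 0.866. The RR moves towards 1, which favours a non-inferiority claim. Counting all as failures leaves 0.866. Neither tests whether removal differed by arm.

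**The case against.** Excluding lesions that are not BCC is defensible. The trial concerns BCC, and a lesion that is not BCC cannot show BCC clearance or recurrence. That stands: the weakness is only that the test may differ by arm.

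The specimen difference is partly inferred. The 25% limit is qualified by the word usually and describes the whole trial, not cream participants at these three centres. The article does not say which tissue is read in the surgery arm. Its remark that a "histological sample may have missed infiltrative nature of lesion" concerns growth pattern, not a missed BCC. This also stands: what is stated is the difference in occasion; the difference in specimen is a natural reading.

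The separate analysis plan is not shown and may contain suitable sensitivity runs. True, so I do not say that none is planned. But the exclusion rule is fixed in this article, and the analyses described beside it do not test it.

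Three stronger readings are tempting and fail:

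- A reader might infer that surgery participants who never have the operation, and so have no histology, are removed too. The rule covers only those found not to have BCC.
- A reader might infer that excluded participants who had surgery are lost from safety reporting. The safety section analyses participants by treatment received, and adverse events are collected from all participants up to the 1 year visit.
- A reader might want re-randomised patients analysed at their first allocation. The rule describes a change of study lesion after the first proved not to be BCC, so that allocation has no BCC outcome to analyse.

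**Conclusion.** The point holds in a limited form. At three of 12 centres, eligibility is settled after allocation by a test whose occasion, and probably specimen, depends on arm, and the analysis set is then conditioned on the result. Randomisation does not protect the comparison there.

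Size and direction cannot be derived from the article. The figures above rest on assumed centre shares, miss rates and prognosis. The largest shifts need half of all participants at these centres and a 20% miss rate. A reader might infer from the table that the exclusions could overturn the trial's conclusion. The document does not support that: the illustration starts at 0.866, already next to the margin, so any small shift appears to cross 0.87, and the decision uses the lower confidence limit, not the point estimate. The effect is probably small. This is a cheap improvement and does not invalidate the design.

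**What to change.** Add to the Statistical analysis section:

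1. A sensitivity analysis repeating the primary analysis in the nine centres that biopsied before randomisation. Identify them explicitly, since the nine smallest centres pooled for adjustment need not be the same nine.
2. A table of post-randomisation exclusions and re-randomisations by arm and centre, with the specimen on which each exclusion was based.
3. If exclusions differ by arm, a bound that is conservative for non-inferiority, for example the excess exclusions in the cream arm counted as cream failures. Do not count excluded participants as successes in both arms.

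The cost is one or two extra model runs and one table, with no change to trial conduct. The downside is precision. If the three centres hold a share s of participants, the nine-centre interval widens by about 1/√(1 − s): 1.05 times at 10%, 1.15 at 25% and 1.41 at 50%. It should be read as a check on consistency with the main estimate, not as a second non-inferiority test.

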**Missing data:** 
sensitivity analyses assuming both worst and best case scenarios will be performed for the primary outcome measure. **Potential outliers** will be identified by range checks and subjected to standard query generation and resolution. In order to **minimise loss of efficiency** in the analysis, the nine smallest centres will be pooled together to form a composite centre.

**Non inferiority margin:** This is based on a 97% success rate for surgery and a lower 98% confidence boundary of 84% for Imiquimod cream. This gives a non-inferiority margin (lower boundary of a 98% confidence interval for the relative difference expressed as a relative risk (imiquimod relative to surgery)) of 0.87. This margin was determined by the clinical judgement of the 4 clinicians who sit on the Trial Steering Committee. The non-inferiority margin will only apply to the analysis of the primary outcome for which non-inferiority is hypothesized.

Two-sided 98% confidence intervals for all outcomes will be presented. Results will be declared significantly "non-inferior" (primary outcome only) if the lower 98% confidence interval for the imiquimod effect relative to surgery is greater than the non-inferiority margin (0.87). Greater confidence will be placed on the results (primary outcome only) if the conclusions from the intention to treat (ITT) and per protocol (PP) analysis are consistent.

Data analysis will remain blinded until all data analysis has been performed and has been checked and approved by the Data Monitoring Committee.

#### Primary outcome measure

The number and percentage of participants successfully treated at 3 years in each treatment group, the absolute difference in percentages between groups and the corresponding 98% confidence interval for the absolute difference in percentages will be reported. The relative risk will be used to indicate the risk of being treated successfully in the imiquimod group relative to the surgery group. Poisson regression with a robust error variance will be used to estimate treatment effect, with centre and BCC type (fixed effects) included as covariates. This approach has been shown to be a reliable method to use for estimating adjusted relative risks for prospective studies with binary outcome variables [16].

Two separate analyses will be undertaken:

i) Adjusting for centre and tumour type

ii) Adjusting for centre, tumour type, tumour size, tumour site and immunosuppression.

#### Secondary outcome measures

**Clinical success **at 1, 2 and 5 years will be analysed and presented in the same way as for the primary outcome variable.

**Time to first recurrence (five categories):** Comparison of treatment groups will use ordinal regression analysis, adjusting for centre and BCC type (fixed effects). The number and percentage of participants in each of the 5 time of first recurrence categories will be reported by treatment group. The odds ratio arising from the continuation ratio model and the corresponding 98% confidence interval will be reported.

**Cosmetic appearance** of lesion site at 6 months and at 3 years as rated by the participant and by an independent dermatologist. The analysis of primary interest will be the participants rating at 6 months, focusing on head and neck, and then on all sites. The analysis of the dermatologist's ratings will be based on lesions at all sites. For each of the cosmetic appearance outcome measures, the number and percentage of participants with a lesion of excellent or good appearance in each treatment group, the absolute difference in percentages between groups and the corresponding 98% confidence interval for the absolute difference in percentages will be reported. The relative risk of having a lesion of excellent or good appearance in the imiquimod group relative to the surgery group and the corresponding two-sided 98% confidence interval will be presented. The inclusion of baseline variables in the model will be explored.

**Level of pain:** for each of the treatment period and the 16 week follow-up period, the number and percentage of participants who experience the following levels of pain (moderate or more severe, mild-moderate or less severe pain, no pain) will be reported by treatment group. The median number of days of moderate or more severe pain will also be reported.

**Cost effectiveness** for the different treatment modalities will be explored.

**Treatment compliance** in the imiquimod group will be reported. The amount of imiquimod cream used will be estimated from the daily diary (number of days of exposure). Insufficient exposure to imiquimod cream will also be reported (<4 weeks treatment for superficial BCCs; <8 weeks treatment for nodular BCCs), also the number unable to complete the full course as a result of an adverse event. In the surgery group treatment compliance will be the receipt of excisional surgery.

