#### Secondary

i) The proportion of participants with clinical success at one, two and five years.

ii) Time to first recurrence (classified into one of the following 5 categories according to the period between follow up visits when this occurred: "prior to year 1 visit"; "between year 1 visit and year 2 visit"; "between year 2 visit and year 3 visit"; "between year 3 visit and year 5 visit"; "no recurrence prior to year 5 visit"). The actual time of recurrence is not known, but only the visit at which it is diagnosed.

iii) The proportion of participants with a lesion of excellent or good appearance at 6 months and at 3 years. (The cosmetic appearance of a participant's lesion will be rated independently by the participant and blinded observer. using a five point scale ("Excellent", "Good", Fair", Poor", "Very poor")).

iv) The proportion of participants experiencing a moderate or more severe level of pain a) during treatment and b) in the 16 weeks following treatment. (This will be measured daily using a six-point scale ("No pain", "Mild", "Mild-Moderate", "Moderate", "Moderate-Severe", "Severe") using a questionnaire completed at home).

v) Cost effectiveness to include number of participant visits to hospital, as well as cost of treatment per session.

Clinical clearance will not be routinely confirmed by further biopsy mainly because a) this would not happen in clinical practice and b) participants benefitting from an excellent cosmetic result in the cream group are unlikely to want a biopsy scar. If, however, the clinician is concerned there is a recurrence, then he/she will biopsy that lesion exactly as would happen in routine follow-up care from other treatment modalities.

**Adverse events **will be collected from all participants up to the 1 year visit, thereafter only events considered serious or related to the trial comparators (imiquimod or surgery) will be collected.

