### Follow-up of outcome measures

The nurse will make a telephone call to the participant at two weeks to discuss any early problems, followed by clinic follow-up at 6, 12, and 18 weeks, 6 months, 1, 2 and 3 years. The dermatologist will also see the participant briefly, at 12 weeks (surgery only), 18 weeks (superficial, imiquimod only), 6 months (nodular, imiquimod only), 1, 2 and 3 years. A postal follow-up of documented recurrences at 5 years will be conducted by writing to GPs, hospital clinics and obtaining pathology records. See figure 1.

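### Time to first recurrence has five closed categories, none of which fits a participant lost or dead without recurrence before year 5, and its last boundary is a visit that does not take place

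*Protocol article*

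**What the plan says.** All references are to the protocol article.

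- **Outcome measures, Secondary, item ii.** Each participant's time to first recurrence is "classified into one of the following 5 categories according to the period between follow up visits when this occurred". Four categories are recurrence intervals, and the only one without an event is "no recurrence prior to year 5 visit". The article explains the grouping: "The actual time of recurrence is not known, but only the visit at which it is diagnosed".
- **Statistical analysis, Secondary outcome measures.** "Comparison of treatment groups will use ordinal regression analysis, adjusting for centre and BCC type (fixed effects". For description, "The number and percentage of participants in each of the 5 time of first recurrence categories will be reported by treatment group". For the effect measure, "The odds ratio arising from the continuation ratio model and the corresponding 98% confidence interval will be reported".
- **Same section, clinical success.** Success "at 1, 2 and 5 years will be analysed and presented in the same way as for the primary outcome variable".
- **Follow-up of outcome measures.** Clinic follow-up ends at 3 years. After that, "A postal follow-up of documented recurrences at 5 years will be conducted by writing to GPs, hospital clinics and obtaining pathology records".
- **Statistical analysis.** Secondary efficacy analyses use the Full Analysis Set. The worst-case and best-case approach to missing data is given for the primary outcome only.

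**The concern.** The outcome is defined as if everyone's status were known to year 5. A participant who leaves, or dies, recurrence-free after the year 2 visit is known to have passed two intervals without recurrence, but no category can record that. With one category per participant, the percentages can be produced only by leaving such people out or by assigning them somewhere. The natural place is the last category, which turns unknown status into success.

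The last category has a further weakness. It is bounded by a visit, but year 5 is a search of GP, hospital and pathology sources for documented recurrences. Such a search can return a recurrence. Unless replies are tracked, it cannot tell a participant who is recurrence-free from one who was not traced. The same applies to clinical success at 5 years.

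The article justifies its long follow-up by the risk of late recurrence, and this outcome is meant to show it. Participants are not masked to two very different treatments, so equal loss between arms cannot be presumed.

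**Working it through.** **Plan's own figures.** The article gives no figure for this outcome. Its only figure on loss is the 10% drop-out in Sample size, which belongs to the original total of 740 for the primary outcome. That total reproduces: (2.326 + 0.842)² × (0.97×0.03 + 0.90×0.10) / (0.13 − 0.07)² = 332.03, so 333 per arm and 666 in all; 666/0.90 = 740. Applied to the revised 500, 10% is 50 participants. No figure is given for loss by year 5.

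**Assumptions for the illustration (not in the documents).** There are 250 per arm and four intervals, with a 1% recurrence risk per interval with surgery. The true odds ratio is (0.10/0.90)/(0.03/0.97) = 3.593, taken from the 90% and 97% success rates in Sample size. Loss is independent of recurrence. It starts after the year 1 visit and removes a fixed fraction of those still at risk at the start of each later interval: 3.4% each time for about 10% in total, 7% each time for about 18% to 19%, and 10%, 10% and 15% for about 30%.

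Interval odds with imiquimod: 3.593 × 0.01/0.99 = 0.0363, a risk of 0.0350. True five-year recurrence is 1 − (1 − 0.0350)⁴ = 13.3% with imiquimod and 1 − 0.99⁴ = 3.9% with surgery.

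**Step 1: category percentages, imiquimod arm.**

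- About 10% loss: 31.6 recurrences, 23.0 lost, 195.4 recurrence-free at year 5. Lost dropped: 31.6/(31.6 + 195.4) = 13.9%. Lost coded recurrence-free: 31.6/250 = 12.6%.
- About 30% loss: 28.4 recurrences, 72.4 lost, 149.3 recurrence-free. Lost dropped: 28.4/(28.4 + 149.3) = 16.0%. Lost coded recurrence-free: 28.4/250 = 11.4%.

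**Step 2: odds ratio.** A continuation ratio (logit) model was fitted to the expected counts in three ways.

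| Lost, surgery / imiquimod | Person-interval, censored | Lost dropped | Lost coded recurrence-free |
|---|---|---|---|
| 10% / 9% | 3.593 | 3.589 | 3.585 |
| 31% / 29% | 3.593 | 3.576 | 3.572 |
| 10% / 18% | 3.593 | 3.806 (+5.9%) | 3.388 (−5.7%) |
| 19% / 9% | 3.593 | 3.381 (−5.9%) | 3.786 (+5.4%) |

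The standard error of the log odds ratio in the third row is about 0.378. The largest shift, ln(3.806/3.593) = 0.058, is about 0.15 of a standard error.

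**Step 3: year 5.** The category list ends at a year 5 visit, and the article says that what is known is the visit at which recurrence was diagnosed. The follow-up section has no clinic visit after year 3. The exclusion criteria require availability for 3 years only. The interval from year 3 to year 5 is therefore the one whose status is least assured, and its end point is misdescribed.

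**The case against.** Four objections deserve weight.

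*The model does not force the choice.* A reader might infer that ordinal regression must either drop the lost participants or call them recurrence-free. That is not so. The article names the continuation ratio model, which conditions on reaching each interval. It can use a participant's completed intervals and censor afterwards, and in that form it returned the assumed odds ratio in every row of the table. The difficulty lies in the one-category-per-participant definition and in the percentages promised on it. This objection stands.

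*Handling rules belong in the separate analysis plan.* The article says full details are there, and it is not shown. A missing censoring rule is therefore no finding, and nothing in the article says that lost participants are dropped or recoded. This too stands. But the closed list and the year 5 visit are stated in the article, and a handling rule elsewhere would not make them correct.

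*The odds ratio is hardly affected.* A reader might infer that loss as such biases it. If a fraction l of recurrence-free participants is dropped in both arms, the factor (1 − l) cancels from the odds ratio for any recurrence. With assumed recurrence of 20% and 3% and l = 0.2, (0.20/0.80)/(0.03/0.97) = 8.08 and (0.20/0.64)/(0.03/0.776) = 8.08. Larger shifts in the percentages can be obtained by supposing that only never-recurring participants are lost: 0.133/(0.133 + 0.867×0.9) = 14.6% instead of 13.9%. But loss also removes people who would have recurred later.

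*The record search is active enquiry.* It may recover people lost to clinic, and excluding those with life-threatening disease or unavailable for 3 years limits early loss. A reader might infer that absence of a record will be scored as success. The article does not say so, and the shared wording for 1, 2 and 5 years concerns the method of analysis. What remains is that the definition leaves this open to confusion.

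**Conclusion.** The point holds as a defect in how one secondary outcome is defined, with a related ambiguity in 5-year success. The five categories have no valid place for a participant whose recurrence-free follow-up ends before year 5, and the final boundary is called a visit when it is a record search.

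The size is modest. Under the stated assumptions, a true 13.3% recurrence is reported 0.6 points too high or 0.7 too low at about 10% loss, and 2.7 points too high or 1.9 too low at about 30%. The odds ratio is essentially unchanged with equal loss and moves by 5% to 6% with roughly twofold unequal loss, which is small against its sampling error. These figures rest on assumed hazards and on loss independent of recurrence; loss that depends on recurrence was not examined. The documents do not support a claim that the planned model is invalid or that its odds ratio is biased as such. The primary outcome at 3 years is not touched. The change is worth making because it is nearly free and keeps unknown status apart from success.

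**What to change.** 1. Define the outcome as the interval of first recurrence or, if there is none, the last interval known to be recurrence-free.
2. Fit the continuation ratio model already planned to person-interval data: one record per participant for each interval with known status, censored after the last. Keep the adjustment for centre and BCC type and the 98% interval. The odds ratio can stay as the effect measure; a complementary log-log link is optional.
3. Replace the five-category percentages with a table by arm and interval showing numbers at risk, recurred and lost, with deaths shown separately.
4. Where no year 5 reply or record is obtained, censor at the last clinic visit attended, at most year 3.
5. Rename the year 5 boundary as the record search. Report time-to-recurrence and clinical success results at year 5 as no documented recurrence among those traced, with the number traced in each arm.

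The cost is slightly more data preparation and wording changes for one secondary outcome and the 5-year success outcome. The model family is unchanged. The only added record keeping is whether a year 5 reply or record was obtained, if that is not already noted.
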